##### Social support

Social support will be measured using the Medical Outcomes Study (MOS) Social Support Survey, a 19-item questionnaire measuring the availability of support in different life domains. The scale was evaluated to be reliable (all Alphas >0.91) and valid (25).

##### Resilience

The Brief Resilience Scale (BRS) measures the ability to bounce back from stressful situations in life (26). BRS is a 6-item questionnaire measuring resilience on a five-point scale ranging from one (low resilience) to five (high resilience). The scale exhibits good internal consistency with Cronbach's α = 0.71 (27).

The project team will measure customer satisfaction regarding the services at the end of the follow-up measurement using a set of questions measuring overall efficiency, professionalism, accessibility, and the overall administration of benefits.

### Intervention components

#### Intervention group: ABFT model of intervention

Participants allotted to the intervention group will receive 12 sessions of biweekly interventions spread across 6 months. Following the baseline assessment, the initial sessions will include two psycho-educative sessions for both patient and family members, focusing mainly on post-hospital engagements and crisis intervention. The introductory sessions will focus on detailed Bio-Psycho-Socio-Cultural-and-Economic assessments exploring the stressors, current coping strategies, and social support, and addressing the priority issues and crisis domains through psychological first aid. The initial sessions are followed by Attachment-Based Family Therapy involving the patients and their significant family member(s) using a structured intervention module. The intervention module will have four major components; relational reframe, developing alliance, repairing attachment, and promoting autonomy (14). Selected social work trainees from educational institutions geographically close to the selected clusters will be trained to use the module to intervene with the participants. Telephonic interventions will be provided to the recruited participants through eight different sessions focusing on various aspects. The first two sessions of telephonic intervention focused on relational reframing. The subsequent sessions are on developing therapeutic alliance work in different family contexts. The following two sessions on repairing attachment work or attachment tasks focus on improving the patient's psychosocial functioning at home and in the community. The final sessions promote autonomy by introducing more respectful and regulated interpersonal problem-solving strategies to tackle different life areas.

The last sessions of the intervention focus on facilitating the linkages with formal and informal community resources available in their locality. The intervention's various components and delivery mechanisms are detailed in Table 2.

**Table 2 T2:** Intervention components.

**Intervention**	**Intervention components**	**Delivery**	**Human resource**
Hospital-based engagements and crisis intervention (2 sessions)	**Psycho-education Focus**-detail Assessment and psychological first aid **Session 1** • Comprehensive assessment of stressors, coping and social support, and instant emotional support through empathetic listening and validation • Psycho-education to the participants and their immediate carers about phenomenology and symptomology of suicidality **Session 2** • Addressing practical issues and use of behavioral and cognitive strategies	Direct	Social workers
Attachment-based family therapy (8 sessions)	**Relational reframe** **Focus**-Environment modification **Goals:** -Improved family communication, and using family members as change agents **Session 1:** • Identifying and articulating the unhelpful patterns in the family • Strengthening the family to address the trust ruptures, inducing a compassionate tone in conversations. **Session 2** • Revisiting current coping strategies and encouraging open and empathic conversations **Developing alliance** **Goals:** -Addressing core family conflicts and providing family members with emotional coaching the skills **Session 3:** • Identifying strengths of the clients, and Problem procedure analysis **Session 4:** • Cognitive, behavioral and emotional strategies **Repairing attachment** **Focus on clarification** **Goals:** Repairing attachment work, improving clients' psychosocial functioning, and working through attachment ruptures through attachment tasks. **Session 5:** • Direct and open communication encouraged • Working through the concerns of family members and their lives and developing trust. Emotional coaching to the family members. **Session 6:** **Strategies** • Appropriate mutual sharing is encouraged to foster mutual intimacy, mutual respect and shared responsibilities **Promoting autonomy** **Focus-insight** **Goals**-Promoting autonomy by introducing problem-solving in interpersonal situations, and engagements. **Session 7 and 8:** • Family encouraged to support the client; Social support improved • Family resources mobilized to address their unmet needs and practical requirements.	Telephonic	Social work trainees (supervised by the multidisciplinary project team)
Linkages with formal and informal Community Resources (2 sessions)	**Connecting with resources to ensure continued support** **Session 1 and 2:** **Focus**–Referral and follow up **Goals**-To facilitate the linkages with locally available formal and informal community resources Strategies: - Linking with Government welfare Departments, Non-Government, Voluntary or Philanthropic Organizations, Economic (job pool), Religious and Social resources (neighborhood groups, community, and religious organizations)	Telephonic	Social work trainees (supervised)

#### Control group: Treatment as usual

Participants recruited to the control group will receive usual care from the hospital. The usual treatment consisted of the medical management of the injuries and referral to various medical specialities and services based on their needs. Often, emphasis on the medical model makes the health system insensitive to the critical psychosocial factors associated with self-harm behavior. In Kerala, the family members or significant people accompany them and motivate them to continue the treatment. However, the option of after-treatment care will be available to patients from both groups, but they will not be assertively engaged with the intervention care package. Psychoeducation about the need for pharmacological treatment will continue in both groups whenever relevant. The family will be given additional information about the early warning signs of suicidal thoughts and ideation to their family members to detect the risk and suicidal intent. Baseline, interim, and follow-up measurements will be done using the same standardized tools for both groups.

### Human resource

The multidisciplinary team for the development and implementation of the project includes

the lead investigators,medical professionals of the department of critical care and emergencies,professional mental health team in the hospitals and SWTs.

Social Work Trainees specializing in medical and psychiatric social work will be recruited from the educational institutions based on their readiness to volunteer for this project. The volunteered trainees will be placed in the emergency departments of the hospitals as part of their field practicum under the supervision of the mental health team and the project lead in implementing the intervention. The trainees will be encouraged to refer their participants, if necessary, to the mental health team for pharmacological and other intense therapeutic interventions.

### Statistical analysis plan

#### Sample size and power calculation

A sample size of 282 will be collected from 10 clusters, with an average of 28 required from each of the 10 clusters. The clusters receiving the FASE intervention and the clusters receiving the usual care will be randomized 1:1 ratio and 28 samples will be recruited for the study allowing for a 20 % loss in follow-up rate. The Critical z is 1.64 and *R*^2^ is 0.3 with 95% power, a two-sided alpha of 5% with a cluster effect of 0.05 results in a sample size of 256. The 95% power and additional 10% respondents would allow us to maintain at least the 80% power even after the 20% loss to follow-up. Thus, we aim to recruit 282 participants for this study.

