### Objectives of the study

The major objectives of the study include

Evaluate the contribution of psychosocial factors to self-harm behavior and the role of psychosocial aspects in preventing suicide.Develop the ABFT and Community Linkage model for the prevention of suicide in a group of people presenting with self-harm behavior at emergency departments;Compare the treatment (TAU) as the usual plus FASE intervention with the TAU using a cluster RCT design framework;Develop the systems and processes appropriate to deliver the services for people presenting with self-harm behavior at emergency to integrate a psychosocial intervention that would have broad relevance and application nationally and in low and middle-income countries;Assess the proposed model's cost-effectiveness for managing self-harm behavior focused on a seamless continuum of care from acute health to community services.

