#### Primary outcome

The primary outcome will be the total suicidality score measured by the Depressive Symptom Inventory–Suicidality Subscale (DSI-SS) (21). The DSI-SS is a 4-item self-report questionnaire designed to assess the frequency and intensity of suicidal ideation and impulses in the past 2 weeks. The scale measured suicidality on a four-point scale ranging from 0 to 3, with higher scores indicating greater severity of suicidal ideation. DSI-SS scores exhibited good internal consistency, ω = 0.90 [95% CI =0.89–0.91], convergent validity (rs = 0.52–0.74), discriminant validity (rs = 0.12–0.27) (22).

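### The 95% power is built on a normal critical value and R² = 0.3; it is not tied to a FASE-versus-TAU difference in DSI-SS and does not hold for a comparison of 5 with 5 hospitals

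*Protocol article*

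**What the plan says.** Under Sample size and power calculation, the protocol article gives the inputs in one sentence: "The Critical z is 1.64 and *R*^2^ is 0.3 with 95% power, a two-sided alpha of 5% with a cluster effect of 0.05 results in". The figure obtained is 256. The article adds 10% to reach 282 and expects this to leave at least 80% power after 20% loss to follow-up. On the design it says: "A sample size of 282 will be collected from 10 clusters, with an average of 28 required from each of the 10 clusters". The clusters are randomised 1:1.

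Under Primary outcome: "The primary outcome will be the total suicidality score measured by the Depressive Symptom Inventory–Suicidality Subscale (DSI-SS"). Under Objectives of the study, the comparison is: "Compare the treatment (TAU) as the usual plus FASE intervention with the TAU using a cluster RCT design framework". The Abstract and Study setting make the hospital emergency department the randomised cluster.

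The Data analysis section plans multiple regression, aimed at overall model fit and the contribution of each predictor.

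**The concern.** Power is a statement about a particular effect on a particular outcome under a particular test. Two things in the printed calculation do not match the trial.

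- **The effect.** The only effect-type input is R² = 0.3. R² describes how much variance a regression model explains. It is not a FASE-minus-TAU difference in DSI-SS, and no such difference, SD or standardised effect is printed.
- **The reference distribution.** A normal critical value treats the number of randomised units as large. Here 10 hospitals are randomised, 5 to each arm, so the arm comparison has 10 − 2 = 8 degrees of freedom.

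The second mismatch is separate from the contradiction between z = 1.64 (the one-sided 5% value) and the stated two-sided alpha. It remains after z is corrected to 1.96.

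At stake is how a null result would be read. A reader who takes the 95% at face value would treat a null finding as strong evidence of no effect on suicidality, although the document does not say which effect the 95% refers to.

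**Working it through.** **Inputs from the article.** Critical z 1.64; R² 0.3; power 95%; two-sided alpha 5%; cluster effect 0.05; N = 256, raised to 282; 10 clusters at 1:1; 20% loss.

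**Inferred.** The cluster effect is read as an ICC. The 1:1 ratio gives 5 v 5 hospitals and 8 df. Cluster sizes are taken as equal; unequal sizes would lower the power figures.

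**1. Reproducing the plan's figures.**
- 256 × 1.1 = 281.6, so 282 follows from 256.
- 256 does not follow from the stated inputs. With R² = 0.3 as the effect tested, f² = 0.3/0.7 = 0.4286. The F-test at 5% and 95% power needs N = 33, 53, 67 or 89 for 1, 5, 10 or 20 predictors.
- The design effect is 1 + (25.6 − 1) × 0.05 = 2.23 for 256 in 10 clusters, or 1 + (28 − 1) × 0.05 = 2.35 for 28 per cluster. The range becomes 33 × 2.23 ≈ 74 to 89 × 2.35 ≈ 209, still short of 256.
- With R² as a covariate term in a logistic z-test, 256 can be reached, but only by adding inputs the article does not give (for example a binary exposure, a 30% event rate, an odds ratio of 3 and a two-sided test). That setting is also for a binary outcome, not a DSI-SS total score.

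**2. Carrying the 95% over to 8 df.** Grant that 256 contains the cluster effect and gives 95% power in a z-test. The implied noncentrality is z(1 − α) + z(0.95):
- from 1.96: 1.960 + 1.645 = 3.605
- from the printed 1.64: 1.645 + 1.645 = 3.290

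Power is then read from the noncentral t on 8 df with two-sided critical value 2.306. For other numbers analysed, with m per hospital, the noncentrality is scaled by the ratio of standard errors, using SE = √[2 × (1 + (m − 1) × 0.05) / (5m)].

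| Analysed | m per hospital | SE (SD units) | Power from z = 1.96 | Power from z = 1.64 |
|---|---|---|---|---|
| 256 | 25.6 | 0.187 | 88.3% | 82.1% |
| 282 × 0.8 ≈ 226 | 22.56 | 0.192 | 86.5% | 80.0% |
| 282 (no loss) | 28.2 | 0.183 | 89.5% | 83.5% |

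**3. What the design can detect on DSI-SS.** On 8 df, two-sided 5%, the noncentrality needed is 3.201 for 80% power and 4.137 for 95%.
- 226 analysed: 3.201 × 0.1919 = 0.61 SD (80%); 4.137 × 0.1919 = 0.79 SD (95%).
- 256 analysed: 3.201 × 0.1867 = 0.60 SD (80%); 4.137 × 0.1867 = 0.77 SD (95%).
- 226 analysed, if covariates explain 30% of the variance at both patient and hospital level (an assumption): multiply by √0.7 = 0.837, giving 0.51 and 0.66 SD.

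**4. Power for assumed differences.** The article gives no difference, so these are illustrations without covariate credit. With 226 analysed, power is 28%, 45% and 63% for 0.3, 0.4 and 0.5 SD, and 89% and 95% for 0.7 and 0.8 SD.

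**The case against.** **No effect size means no ceiling.** A reader might infer that the trial's power is at best 88%. The article does not support that. The 88% takes the 95% as a true noncentrality and moves it to 8 df. With all 282 analysed it is 89.5%, and a difference of about 0.77 SD with 256 analysed would have 95% power. This objection stands, and the 88% and 82% are conditional illustrations only.

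**The fallback survives.** The article does not promise 95% at analysis; it promises at least 80% after 20% loss. With 226 completers the figures are 86.5% or 80.0%, so that promise is roughly kept. This also stands. It does not rescue the printed 95%.

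**Clustering is stated to be inside 256.** A reader might suppose the design effect was left out, which would put power near 50%. The text says otherwise: "with a cluster effect of 0.05 results in a sample size of 256". That reading is not pursued.

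**The effect may sit in the full protocol.** A critical z with an R² fits a regression z-test in which R² is a covariate term, and the treatment effect may simply be unprinted. An article may condense, and the form of the test is an inference. So one cannot say that the underlying calculation ignored the arm difference. What can be said is that the article prints inputs, a result and a power claim, and that these inputs neither give the result nor attach the claim to DSI-SS.

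**The 8 df are inferred.** The reference distribution for the arm test is commonly left to the analysis plan. But 10 clusters and 1:1 are printed, and a power figure based on a normal critical value does not fit so few randomised units.

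**Conclusion.** The point holds in this form: the printed 95% power does not belong to the FASE-versus-TAU comparison of DSI-SS. The stated inputs do not reproduce 256 and name no DSI-SS difference. A normal-based 95% falls to about 88% (from z = 1.96) or 82% (from z = 1.64) on 8 df with 256 analysed, and to about 87% or 80% with 226.

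This rests on reading the cluster effect as ICC 0.05, on 256 already including it, on equal cluster sizes and on a 5 v 5 split. It does not show that the trial is too small. Whether 282 is adequate depends on the DSI-SS difference worth detecting, which the article does not give.

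**What to change.** Keep the recruitment target of 282 and delete the unqualified 95%. Replace the R²/critical-z sentence with a calculation for the primary comparison: difference in mean 6-month DSI-SS total, 5 v 5 hospitals, ICC 0.05, two-sided 5%, t reference on 8 df, about 22.6 analysed per hospital (226 in all).

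Suggested wording: *With 282 recruited in 10 hospitals and 20% loss, about 226 participants will be analysed. Assuming an ICC of 0.05 and a two-sided 5% test on 8 degrees of freedom, this gives 80% power for a difference of about 0.61 SD in DSI-SS total score and 95% power for about 0.79 SD.*

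If 256 are expected to be analysed, the figures are 0.60 and 0.77 SD. Any credit for R² = 0.3 as covariate adjustment should be stated as an assumption, including that it applies at both levels (about 0.51 and 0.66 SD with 226 analysed).

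The Study procedure section gives a different target, 158. That is a separate inconsistency, to be reconciled in the same edit.

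The cost is a rewritten paragraph and a less favourable stated power. No patients or hospitals are added.

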#### Data analysis

Hard copies of data will be stored in a secure place, while soft data will be stored securely using file locks and passwords. Basic descriptive statistics will be computed for outcomes. The main effects of the interventions will be assessed on primary and secondary outcomes at different time points before and after the intervention. With the SPSS and R software, we will run the multiple regression modeling to determine the overall fit of the model and the relative contribution of each of the predictors to this variance. Multinomial Logistic Regression will be applied to study the exposure variables that are likely to contribute to the variation on the outcome variables, and discriminant analysis will be used to determine whether the clusters differ with regard to the predictors.

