### Outcome

Study outcomes are assessed at baseline and 6-month follow-up. Demographic characteristics measured at baseline include age, gender, marital status, education, occupation, and family income. The following information on the clusters selected will be collected: number of hospital beds, patients, social workers, primary treatment modalities, and the average length of stay at the hospital. Measurement domains and time points are summarized in Table 1.

**Table 1 T1:** Measurement domains and data collection time points.

**Variable**	**Dimensions included**	**Measurement tool**	**Data collection time points**		
			**Baseline (T0)**	**3 months (T1)**	**6 months (T2)**
Demographic assessment	Age, sex, marital status, education, occupation, and family income		✓		
Suicidality	Suicidal thoughts and ideation	Depressive Symptom Inventory–Suicidality Subscale (DSI-SS)	✓	✓	✓
Depression, anxiety, stress	Depression, anxiety, stress	DASS 21	✓	✓	✓
Social support	Emotional support, tangible support, affectionate support, positive social interaction	The MOS social support survey	✓		✓
Resilience	Resilience	The Brief Resilience Scale (BRS)	✓		✓
Customer satisfaction		Questionnaire			✓

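### The regression named in the analysis section targets model fit and shares of variance, which suit the first objective; no named method targets the FASE-versus-usual-care difference in DSI-SS

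*Protocol article*

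**What the plan says.** All references are to the protocol article.

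- **Objectives of the study**, third objective: "Compare the treatment (TAU) as the usual plus FASE intervention with the TAU using a cluster RCT design framework".
- **Primary outcome**: "The primary outcome will be the total suicidality score measured by the Depressive Symptom Inventory–Suicidality Subscale (DSI-SS").
- **Data analysis**, on the intervention effect: "The main effects of the interventions will be assessed on primary and secondary outcomes at different time points before and after the intervention". No model, contrast or test is attached.
- **Data analysis**, on multiple regression: "we will run the multiple regression modeling to determine the overall fit of the model and the relative contribution of each of the predictors to" the variance.
- **Data analysis**, on the second model it names: "Multinomial Logistic Regression will be applied to study the exposure variables that are likely to contribute to the variation on the outcome variables".
- **Data analysis**, on the third and last method, which concerns differences between hospitals rather than arms: "discriminant analysis will be used to determine whether the clusters differ with regard to the predictors".
- **Sample size and power calculation**: "The Critical z is 1.64 and *R*^2^ is 0.3 with 95% power". It gives no difference between FASE and usual care, and does not say what the R² describes.
- **Outcome**: "Demographic characteristics measured at baseline include age, gender, marital status, education, occupation, and family income". Whether these variables enter the regression is not stated.

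**The concern.** The trial is randomised to answer one question: does adding FASE to usual care lower DSI-SS more than usual care alone? The matching null hypothesis is a zero between-arm difference.

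Overall fit concerns a different null, that every coefficient in the model is zero. It is false as soon as any predictor is related to later suicidality, whatever FASE does. A predictor's share of explained variance has no sign and is not a mean difference with an interval, so it cannot say whether FASE helped or harmed, or by how much.

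The sentence on main effects does not fill the gap, because its wording is before-and-after. The DASS-21 paragraph leans the same way: it ties effectiveness to a fall in depression scores in both groups, and a fall in both groups is not a difference between them.

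With no between-arm contrast tied to a model, a well-fitting model, a variance share or a within-group change could each be offered later as evidence that FASE works. The abstract expects the results to inform policy and clinical guidelines.

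**Working it through.** **1. Objectives against methods.**

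| Method named in Data analysis | Stated purpose | Objective it serves |
|---|---|---|
| Multiple regression | Overall fit; predictors' share of variance | First (psychosocial contributors) |
| Multinomial logistic regression | Exposure variables related to outcomes | First |
| Discriminant analysis | Whether clusters differ on predictors | Neither first nor third directly; describes cluster differences |
| None named | Main effects, before and after | Third, but no between-arm contrast given |

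**2. Sample sizes.** The article's recruitment figure reproduces from its own base: 256 × 1.10 = 281.6, rounded to 282. The base of 256 cannot be rebuilt, because neither an effect size nor a number of predictors is given. The stated 20% loss leaves 282 × 0.80 = 225.6, about 226. The check therefore uses n = 226 and n = 282.

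**3. How often overall fit is significant when FASE does nothing.**

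Inputs:
- n = 226 or 282, from step 2.
- α = 0.05, from the sample-size section.
- k = 8 predictors, namely arm plus seven baseline variables. This is an assumption.
- R² explained by the baseline variables. This is also an assumption, so a range is shown.
- Arm coefficient = 0.

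Formula: the overall F statistic has k and n − k − 1 degrees of freedom and noncentrality λ = n·R²/(1 − R²). Power is the probability that it exceeds the 5% critical value.

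- n = 226: degrees of freedom 8 and 217, critical F = 1.98. At R² = 0.05, λ = 226 × 0.05/0.95 = 11.89.
- n = 282: degrees of freedom 8 and 273, critical F = 1.97. At R² = 0.05, λ = 282 × 0.05/0.95 = 14.84.

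| Baseline R² | λ (226 / 282) | P(fit significant), n = 226 | n = 282 |
|---|---|---|---|
| 0.02 | 4.61 / 5.76 | 0.26 | 0.33 |
| 0.05 | 11.89 / 14.84 | 0.66 | 0.78 |
| 0.10 | 25.11 / 31.33 | 0.963 | 0.990 |
| 0.30 | 96.86 / 120.86 | 1.000 | 1.000 |

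Varying the assumed number of predictors from 2 to 11 over the same two sample sizes gives 0.23–0.56 at R² = 0.02, 0.59–0.94 at R² = 0.05, and 0.94 to above 0.999 at R² = 0.10.

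**4. The arm coefficient in the same model.** The simulation had 4,000 trials per setting, 10 clusters of 28, arm plus seven baseline covariates and no FASE effect.

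| Intracluster correlation | Ordinary regression, arm coefficient | Cluster-level t test of arm |
|---|---|---|
| 0 | 0.048–0.058 | 0.049–0.052 |
| 0.05 | 0.19–0.20 | 0.044–0.052 |

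The ranges run over baseline R² of 0, 0.05, 0.10 and 0.30. The rejection rate of the arm test shows no trend with baseline R², unlike that of overall fit. The second row reads the article's cluster effect of 0.05 as an intracluster correlation. It shows that ordinary regression on arm would hit the right target with a false-positive rate about four times nominal.

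**The case against.** The strongest reply is that the article never makes overall fit the test of FASE. It names no F test or likelihood-ratio test of fit, sets no significance rule for fit, and says separately that the interventions' main effects will be assessed. The Study procedure section also says that results will be compared with a usual-care group. The regression sentence has a natural home in the first objective, and arm is not excluded from the predictors. Finally, a journal article may leave the exact primary model to a fuller document.

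Much of this stands. A reader might infer that the trial would almost surely declare FASE effective on the strength of a significant model. The document does not support that, for three reasons:
- No such decision rule is stated.
- Near-certain significance needs a baseline R² of about 0.10 or more. At 0.02 it is 26–33% with eight predictors.
- The R² of 0.3 in the sample-size section is not described as variance explained by baseline factors, and it is given beside a critical z, which is not an overall F statistic. The 0.30 row above is therefore an illustration, not the protocol's own scenario.

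The reply does not remove the point. The article does more than leave the model open: it names three methods, gives each a purpose, and directs none of them at the comparison in its third objective. If arm is among the predictors, the stated output is still its share of variance, not a signed difference.

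**Conclusion.** The point holds as a mismatch between question and method. The regression named in Data analysis answers the first objective. The third objective, which is the reason for randomising, has a before-and-after statement and no between-arm contrast.

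On size: with no FASE effect, overall fit would still be significant in about 66–78% of trials at a baseline R² of 0.05 and 96–99% at 0.10. A significant fit therefore carries no information specific to FASE. These figures assume arm plus seven predictors, independent patients, 226–282 analysed, and a 5% test of fit that the article does not itself specify. They measure how uninformative fit is about FASE, not the trial's false-positive rate. The change is worth making because it is nearly free and closes off later choice among fit, variance shares and within-group change as evidence of effectiveness.

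**What to change.** In Data analysis, add a sentence such as: *The primary test is the coefficient of randomised arm (FASE plus usual care versus usual care) on the DSI-SS total at 6 months, adjusted for baseline DSI-SS and allowing for clustering by hospital with a method suited to 10 clusters, reported as a mean difference with 95% confidence interval.* Suitable methods include a cluster-level analysis or a mixed model with small-sample degrees of freedom. The allowance for clustering has to be in the same sentence, given the type I error of 0.19–0.20 for ordinary regression shown above.

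Use the same contrast for DASS-21, the MOS survey and the BRS. Keep model fit, variance shares, and the multinomial and discriminant analyses, labelled as descriptive work for the first objective.

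The cost is a few sentences. Table 1 already schedules DSI-SS at baseline and 6 months, and arm is known by design. The small downside is that fit and variance shares can no longer be presented as evidence of effectiveness.
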